**Number of 500 mg tablets to be taken**

**Surface Area** Total Daily Dose **morning evening**

**(m2) (mg)***

<= 1.08 1000 1 1

1.09‑1.4 1500 2 1

1.41‑1.71 2000 2 2

1.72‑2.02 2500 3 2

***Total Daily Dose rounded to the nearest 500 mg and divided into**

**morning and evening doses.**

**Dose‑Limiting Toxicity**

i) >grade 3 non‑hematologic toxicity, except for diarrhea, nausea, vomiting, fatigue, anorexia, alopecia, fever and/or local reactions.

ii) grade 4 diarrhea lasting >3 days which is not controllable with loperamide or other such medications. Or grade 4 diarrhea that requires IV hydration.

iii) grade 4 neutropenia lasting >3 days

iv) grade 4 thrombocytopenia

v) grade 2 hand foot syndrome. Dose adjustments will be as per the following table:

| **Toxicity NCI Grades** | **During a Course of Therapy** |
| --- | --- |
| *Grade 1* | Maintain dose |
| *Grade 2* | |
| ‑ 1st appearance (non‑HFS) | Interrupt until resolved to grade 0‑1 |
| ‑ 1st appearance of HFS | Interrupt until resolved to grade 0‑1, then continue at 75 % of original dose. |
| ‑2nd appearance | Interrupt until resolved to grade 0‑1, then continue at 75 % of original dose. |
| ‑3rd appearance | Interrupt until resolved to grade 0‑1, then continue at 50 % of original dose. |
| ‑4th appearance | Discontinue treatment permanently |
| *Grade 3* | |
| ‑ 1st appearance | Interrupt until resolved to grade 0‑1, then continue at 75 % of original dose with prophylaxis where possible. |
| ‑2nd appearance | Interrupt until resolved to grade 0‑1, then continue at 50 % of original dose. |
| ‑3rd appearance | Discontinue treatment permanently |
| *Grade 4* | |
| ‑ 1st appearance | Discontinue permanently  or  If physician deems it to be in the patient's best interest to continue, interrupt until resolved to grade 0‑1, then continue at 50 % of original dose . |

Dosage modifications are not recommended for grade 1 events. Therapy withcapecitabine should be interrupted upon the occurrence of a grade 2 or 3 adverse experience. Once the adverse event has resolved or decreased in intensity to grade 1, then therapy may be restarted at full dose or as adjusted according to the above table. If a grade 4 experience occurs, therapy should be discontinued or interrupted until resolved or decreased to grade 1, and therapy should be restarted at 50% of the original dose. Doses of capecitabine omitted for toxicity are not replaced or restored; instead the patient should resume the planned treatment cycles. Once the dose has been reduced it should not be increased at a later time.

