## Toxicity

CAPECITABINE can induce diarrhea, sometimes severe. Patients with severe diarrhea should be carefully monitored and given fluid and electrolyte replacement if they become dehydrated. National Cancer Institute of Canada (NCIC grade 2 diarrhea is defined as an increase of 4 to 6 stools/day or nocturnal stools, grade 3 diarrhea as an increase of 7 to 9 stools/day or incontinence and malabsorption, and grade 4 diarrhea as an increase of >10 stools/day or grossly bloody diarrhea or the need for parenteral support. If grade 2, 3 or 4 diarrhea occurs, administration of capecitabine should be immediately interrupted until the diarrhea resolves or decreases in intensity to grade 1. Following grade 3 or 4 diarrhea, subsequent doses of capecitabine should be decreased. Standard antidiarrheal treatments (eg, loperamide) are recommended. Necrotizing enterocolitis (typhlitis) has also been reported.

Hand‑and‑foot syndrome (palmar‑plantar erythrodysesthesia or chemotherapy induced acral erythema) is characterized by the following: numbness, dysesthesia/paresthesia, tingling, painless or painful swelling, erythema, desquamation, blistering and severe pain. Grade 2 hand‑and‑foot syndrome is defined as painful erythema and swelling of the hands and/or feet and/or discomfort affecting the patient's activities of daily living. Grade 3 hand‑and­foot syndrome is defined as moist desquamation, ulceration, blistering and severe pain of the hands and/or feet and/or severe discomfort that causes the patient to be unable to work or perform activities of daily living. If grade 2 or 3 hand‑and‑foot syndrome occurs, administration of capecitabine should be interrupted until the event resolves or decreases in intensity to grade 1. Following the occurrence of grade 2 handand‑foot syndrome, subsequent doses of capecitabine should be decreased.

There has been cardiotoxicity associated with fluorinated pyrimidine therapy, including myocardial infarction, angina, dysrhythmias, cardiogenic shock, sudden death and electrocardiograph changes. These adverse events may be more common in patients with a prior history of coronary artery disease.

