Patients with mild to moderate hepatic dysfunction due to liver metastases should be carefully monitored when capecitabine is administered. The effect of severe hepatic dysfunction on the disposition of capecitabine is not known. If drug related grade 2‑4 elevations in bilirubin occur, administration of capecitabine should be immediately interrupted until the hyperbilirubinernia resolves or decreases in intensity to grade 1. NCIC grade 2 hyperbilirubinernia is defined as 1.5 x normal, grade 3 hyperbilirubinemia as 1.5‑3 x normal and grade 4 hyperbilirubinemia as >3 x normal.

Increases in adverse events have been noted in patients with reduced renal function. Therefore, patients will be excluded for a calculated creatinine clearance of less than 50 ml/min.

Myelosuppression was rare.

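### The dose table grades toxicity by NCI and the text by NCIC, and bilirubin grades 2 and 3 share the value 1.5 x normal, so one value leads to two restart rows

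*Protocol*

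**What the plan says.** Grades appear in four places in the protocol, under different names or none.

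- **Dose-adjustment table (Dose-Limiting Toxicity section).** The column that selects the dose action is headed "Toxicity NCI Grades". No version is given.
- **Dose-limiting toxicity list (same section).** Its items are stated by grade, with no scale named.
- **Diarrhea (Toxicity section).** The Canadian body is spelled out: "National Cancer Institute of Canada (NCIC grade 2 diarrhea is defined as an increase of 4 to 6 stools/day or nocturnal stools". The band above it covers 7 to 9 extra stools a day, and its alternative criterion is malabsorption with incontinence. The top band is printed with a strict inequality: "grade 4 diarrhea as an increase of >10 stools/day". Gross blood in the stool, or parenteral support being needed, also qualifies for it.
- **Bilirubin (Toxicity section).** "NCIC grade 2 hyperbilirubinernia is defined as 1.5 x normal". Grade 3 runs from 1.5 to 3 x normal, and grade 4 is above 3 x normal. Drug-related elevations of grade 2 to 4 lead to interruption.

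The hand-and-foot syndrome grades in the Toxicity section carry no scale name either. The toxicity of the combination is the secondary objective (Objectives). Eligibility item 11 admits patients with bilirubin up to and including 1.5 times normal.

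**The concern.** A grading scale should give each observation exactly one grade, and one named scale should feed every rule that uses grades. Here the table that selects the dose action names one scale, and the text that defines two of the graded events names another. Because the Canadian body is written out in full, NCIC there does not look like a typing slip for NCI. The bilirubin bands also overlap, whichever scale is meant.

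Two things are at stake. The first is the restart row that applies after an interruption. The second is the grade entered in the data for the secondary toxicity objective. A statistical analysis plan, if one exists, could settle how grades are tabulated. It could not make consistent the decisions already taken from them during treatment.

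**Working it through.** The protocol gives no numerical result to reproduce here. The check assigns each value to the bands as printed, then repeats this under the obvious alternative readings.

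**Bilirubin (multiples of normal).** Inputs from the Toxicity section: grade 2 = 1.5; grade 3 = 1.5 to 3; grade 4 = above 3. No grade 1 band is printed.

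| Value | Grade 2 literally 1.5 | Grade 2 read as above 1, up to and including 1.5 | Grade 2 read as above 1, below 1.5 |
|---|---|---|---|
| 1.4 | none of 2-4 | 2 | 2 |
| 1.5 | 2 and 3 | 2 and 3 | 3 |
| 1.51 | 3 | 3 | 3 |
| 3 | 3 | 3 | 3 |
| 3.01 | 4 | 4 | 4 |

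The double grade at 1.5 survives the inclusive reading. It disappears only if grade 2 stops below 1.5, which is not what is printed. Eligibility item 11 allows entry at exactly 1.5, so a patient can be enrolled on the doubly graded value. The interruption rule covers drug-related elevations only, so such a baseline value does not by itself trigger it.

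**What the tie changes.** From the dose-adjustment table, for a first appearance at 1.5 x normal:
- as grade 2 (not hand-and-foot syndrome): interrupt until grade 0-1, no reduction printed;
- as grade 3: interrupt until grade 0-1, then 75% of the original dose.

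Both rows interrupt. They differ in the restart dose and in the grade recorded.

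**Diarrhea (increase in stools/day, stool count only).** Inputs from the Toxicity section: grade 2 = 4 to 6; grade 3 = 7 to 9; grade 4 = above 10.

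| Increase | As printed | If the sign is 'at least 10' |
|---|---|---|
| 4 to 6 | 2 | 2 |
| 7 to 9 | 3 | 3 |
| 10 | none | 4 |
| 11 or more | 4 | 4 |

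Only the value 10 is affected, and the alternative sign closes the gap. At first appearance the table gives interruption then 75% for grade 3, and discontinuation or, at the physician's judgement, 50% after interruption for grade 4. The Toxicity section interrupts for grade 2, 3 or 4 diarrhea, so the choice between the two neighbouring grades does not decide whether treatment is interrupted.

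**Scale names.** Table: NCI. Diarrhea and bilirubin text: NCIC. Dose-limiting toxicity list and hand-and-foot definitions: none. No sentence equates the two names or ranks them. The NCI scale is not reproduced, so no comparison of cut-offs between the two can be made from the document.

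**The case against.** The strongest reply is that this is a wording problem at two isolated values. Much of that stands, and it limits the point in several ways.

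- **A reader might infer that events are being graded on two different scales.** Two names do not prove two scales. NCI may be shorthand for NCIC, or the scales may agree on these events. The document shows a naming conflict, not a measured difference. The text at hand also shows the heading Appendix 1 without content, so a scale printed there cannot be ruled out.
- **A reader might treat the gap at 10 stools as firm.** It probably is not. In the Assessment of Response table, the top analgesic frequency is more than three times daily, which begins at 4, yet its tablet count is printed as above 4. The same loss of an 'at least' sign would explain the stool band.
- **A reader might infer that interruption is inconsistent.** It is not: each candidate grade at either value leads to interruption.
- **A reader might infer a distorted dose-limiting toxicity count.** The first item of the list is printed as above grade 3, so on a literal reading a tie between grades 2 and 3 cannot change it. If the sign were instead 'at least', the same argument would close the stool gap. In the diarrhea item, the need for IV hydration is largely covered, because parenteral support is grade 4 whatever the stool count. There is one starting dose scheme, and no decision rule uses such a count.
- **A reader might add differences between sites, or lost comparability with the capecitabine experience cited in the Background.** The protocol never says there is more than one centre, and the Background gives no grades or scale for that experience. Nor does the protocol state that toxicity will be reported as frequencies by grade.

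The reply leaves two things untouched: the conflict of scale names, and the bilirubin tie. The latter does not depend on any lost sign and leads to two printed dose actions.

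**Conclusion.** The point holds in a limited form and should be corrected. The protocol names two grading scales without saying which governs, and its bilirubin bands give one value, 1.5 x normal, two grades. For a drug-related elevation at that value, the printed rules lead to two restart rows: no reduction printed, or 75%. The same ambiguity enters the grade recorded for the secondary toxicity objective. The primary objective, pain and narcotic relief, is not touched.

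The demonstrable size is one bilirubin value, plus possibly one stool count if the sign is really as printed. The effect of the scale-name conflict could be nil or larger, and the document gives no means of telling. The conclusion assumes that the bilirubin bands are read as printed and that no section missing from the text at hand settles the governing scale.

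**What to change.** Name one grading scale and its version for the dose-adjustment table, the dose-limiting toxicity list and the secondary toxicity objective, and grade all events on it. Reconcile the diarrhea and bilirubin bands in the Toxicity section, and the rules in the Dose-Limiting Toxicity section, with that scale so that the bands are exhaustive and do not overlap. Check the sign in the grade 4 stool count against the source document before changing it. Which cut-off or dose rule applies is for the clinical team.

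The cost is protocol wording, a case report form header, and re-grading of any events already recorded.

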## Toxicity

CAPECITABINE can induce diarrhea, sometimes severe. Patients with severe diarrhea should be carefully monitored and given fluid and electrolyte replacement if they become dehydrated. National Cancer Institute of Canada (NCIC grade 2 diarrhea is defined as an increase of 4 to 6 stools/day or nocturnal stools, grade 3 diarrhea as an increase of 7 to 9 stools/day or incontinence and malabsorption, and grade 4 diarrhea as an increase of >10 stools/day or grossly bloody diarrhea or the need for parenteral support. If grade 2, 3 or 4 diarrhea occurs, administration of capecitabine should be immediately interrupted until the diarrhea resolves or decreases in intensity to grade 1. Following grade 3 or 4 diarrhea, subsequent doses of capecitabine should be decreased. Standard antidiarrheal treatments (eg, loperamide) are recommended. Necrotizing enterocolitis (typhlitis) has also been reported.

Hand‑and‑foot syndrome (palmar‑plantar erythrodysesthesia or chemotherapy induced acral erythema) is characterized by the following: numbness, dysesthesia/paresthesia, tingling, painless or painful swelling, erythema, desquamation, blistering and severe pain. Grade 2 hand‑and‑foot syndrome is defined as painful erythema and swelling of the hands and/or feet and/or discomfort affecting the patient's activities of daily living. Grade 3 hand‑and­foot syndrome is defined as moist desquamation, ulceration, blistering and severe pain of the hands and/or feet and/or severe discomfort that causes the patient to be unable to work or perform activities of daily living. If grade 2 or 3 hand‑and‑foot syndrome occurs, administration of capecitabine should be interrupted until the event resolves or decreases in intensity to grade 1. Following the occurrence of grade 2 handand‑foot syndrome, subsequent doses of capecitabine should be decreased.

There has been cardiotoxicity associated with fluorinated pyrimidine therapy, including myocardial infarction, angina, dysrhythmias, cardiogenic shock, sudden death and electrocardiograph changes. These adverse events may be more common in patients with a prior history of coronary artery disease.

Patients with mild to moderate hepatic dysfunction due to liver metastases should be carefully monitored when capecitabine is administered. The effect of severe hepatic dysfunction on the disposition of capecitabine is not known. If drug related grade 2‑4 elevations in bilirubin occur, administration of capecitabine should be immediately interrupted until the hyperbilirubinernia resolves or decreases in intensity to grade 1. NCIC grade 2 hyperbilirubinernia is defined as 1.5 x normal, grade 3 hyperbilirubinemia as 1.5‑3 x normal and grade 4 hyperbilirubinemia as >3 x normal.

Increases in adverse events have been noted in patients with reduced renal function. Therefore, patients will be excluded for a calculated creatinine clearance of less than 50 ml/min.

Myelosuppression was rare.

**Assessment of Response**

Pain scores and narcotic scores will be determined using the guidelines in following table:

PAIN AND NARCOTIC CATEGORIES AND SCORES

PAIN ANALGESIA

Severity 0 ‑ No pain 0 ‑ None

I ‑ Mild I ‑ Analgesics (ASA, *Bufferin, Tylenol, Anacin, etc.)*

2 ‑ Moderate 2 ‑ Mild Narcotic, (< 112 gr. *codeine, Darvon, etc.)*

3 ‑ Severe 3 ‑ Moderate Narcotic (> 112 < gr. *codeine, Percoan, etc)*

4 ‑ Strong 4 ‑Narcotic, (> 1 gr. *codeine, demerol, morphine, etc)*

Frequency 0 ‑ None 0 ‑ None

I ‑ Occasional (< *daily)* I ‑ p.r.n. (< *daily)*

2 ‑ Intermittent *(at least daily)* 2 ‑ q.d. (I *tab. or cap./day)*

3 ‑ Frequent (>. I < 3 *daily)* 3 ‑ b.i.d. t.i.d. (> I < 4 *tab. or cap./day)*

4 ‑ Constant *(most of the time)* 4 ‑ > t.i.d. (> 4 *tab. or cap./day)*

Pain Score = Pain Severity Grade x Pain Frequency Grade

**Narcotic Score** = Analgesia Severity Grade x Analgesic Frequency Grade

Response will be evaluated by questionnaires at follow‑up visit at 2, 4 and 8 weeks after completion of radiotherapy and by phone call interviews (when necessary for completeness) in poor compliance patients.

The "worst pain score" will be used as response endpoint. The time to maximal pain relief is the time from the first day of irradiation to the time of the lowest pain score for average pain.

Response Definitions

**Complete response** is defined as an average pain score of 0 for two consecutive analysis periods. Narcotic consumption must not be increased. **Partial response**. A decrease of at least 2 points in the worst pain score for two consecutive analysis periods. Narcotic consumption must not be increased. **No response** (any of the following): A pain score that does not change within 8 weeks from the start of radiation therapy.

A 2 point increase in worst pain score that is sustained at a higher level in the month following the first day of radiation therapy.

A pain score that drops by at least 2 points and subsequent sustained rise *(on 2 successive questionnaires)* of pain score by at least 2 points. Any patient with progressive pain in the treated area should have plain radiographs of the area to assess for bone stability and pathologic fracture.

References.

1.

Hoskin PJ. Scientific and clinical aspects of radiotherapy in the relief of bone pain. Cancer Surv. 7:69, 1988.

2. Tong D, Gillick L, Hendrickson FR. The palliation of symptomatic osseous metastases: the

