**OBJECTIVES**

Hypothesis: Given the hypothesis that regimens employing greater intensity radiation yield higher rates of pain relief, radiosensitization using a tumor targeted drug like Xeloda should improve the rate of complete pain relief as compared to radiosensitization with 5FU alone.

Primary Objective:

To determine the frequency and duration of pain relief and narcotic relief for the proposed regimen.

Secondary Objective:

To determine the toxicity of concurrent Capecitabine and radiotherapy in breast cancer patients with bone metastases.

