**PRETREATMENT EVALUATION**

1. Histologic diagnosis of the primary site.

2. Radiographic assessment, with must include plain x-ray of the index lesion (s) and a bone scane.

3. Pain assessment score (BPI ).

4. Laboratory studis within 2 weeks of registration (CBC, serum ALT, AST ,total bilirubin and creatinine).

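### The baseline pain measure and the response rules share no named scale, and no pretreatment narcotic score is scheduled

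*Protocol*

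**What the plan says.** The Objectives section of the protocol gives the primary objective as "To determine the frequency and duration of pain relief and narcotic relief for the proposed regimen".

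The Pretreatment Evaluation section has four items: histology, radiographs, "Pain assessment score (BPI") and blood tests, the last listed as "Laboratory studis within 2 weeks of registration (CBC, serum ALT, AST ,total bilirubin and creatinine"). The BPI is the only pain measure among them. No item records analgesic type, analgesic frequency or a narcotic score.

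The Assessment of Response section opens with "Pain scores and narcotic scores will be determined using the guidelines in following table". Its two formulas are "Pain Score = Pain Severity Grade x Pain Frequency Grade" and, for narcotics, "Analgesia Severity Grade x Analgesic Frequency Grade". The same section then says that a worst pain score "will be used as response endpoint". Partial response is "A decrease of at least 2 points in the worst pain score for two consecutive analysis periods". Complete response is an average pain score of 0, also at two assessments in a row. Both require that narcotic use has not risen. Time to maximal relief is read from average pain. The no-response rules refer partly to worst pain and partly to a pain score with no qualifier. Questionnaires are scheduled at 2, 4 and 8 weeks after radiotherapy, but the questionnaire is not named.

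**The concern.** Partial response is a change from baseline, so the baseline and follow-up values must be on the same scale. The protocol names one instrument before treatment and describes another for scoring response. It then writes the response rules in terms that the second instrument does not produce, and gives no mapping between the two. Two analysts could follow the text faithfully and report different response frequencies from the same patients.

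The narcotic side has a parallel gap. A condition that narcotic use has not increased needs a pretreatment value, and so does any estimate of narcotic relief, which is half of the primary objective. A baseline value that was not recorded cannot be collected later.

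**Working it through.** The protocol states no sample size, power or expected response rate, so there is no figure to reproduce. The check has two parts.

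**1. What each rule needs against what is scheduled**

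- *Partial response:* needs worst pain at baseline and follow-up on one scale. Scheduled at baseline: BPI. The scoring table gives a single product, with no worst version.
- *Complete response and time to maximal relief:* need an average pain score. The table gives no average version.
- *Narcotic condition and narcotic relief:* need a pretreatment analgesia type grade and frequency grade. Neither is in the pretreatment list. This gap does not depend on which pain scale is meant.

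Two readings are possible. If the rules belong to the BPI, worst and average pain can make sense, but the pain half of the table has no role in response. If they belong to the table, worst and average are undefined and the scheduled baseline is on a different scale from follow-up.

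**2. What 2 points means if the product is the response scale**

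Inputs: severity S and frequency F, each graded 0 to 4 in the table; score P = S × F; threshold 2.

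- Attainable values of P: 0, 1, 2, 3, 4, 6, 8, 9, 12, 16.
- One grade less severity: S × F − (S − 1) × F = F. One grade less frequency: S × F − S × (F − 1) = S. The size of a one-grade improvement therefore depends on the other grade.
- Either one-grade step reaches 2 points when S ≥ 2 and F ≥ 2: 3 × 3 = 9 of the 4 × 4 = 16 non-zero cells.
- Single steps: 16 × 2 = 32. The severity step qualifies in the 12 cells with F ≥ 2 and the frequency step in the 12 cells with S ≥ 2, so 24 of 32 qualify and 8 do not.
- Smallest fall between attainable values that qualifies: 2 from 2, 3, 4, 6 or 8; 3 from 9 or 12; 4 from 16. From 1 there is none, because 1 − 2 is below 0.

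The layout of the extracted table leaves some doubt whether pain severity ends at 3 or 4. If it ends at 3, the value 16 disappears and the count is 2 × 3 = 6 of 3 × 4 = 12 cells.

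As a comparison of scale, 2 points is 2/16 = 12.5% of the product range (2/12 = 16.7% if severity ends at 3). The protocol gives no BPI range. If a BPI item is assumed to run from 0 to 10, 2 points is 20% of it.

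**The case against.** The best reply is that the response rules were written for the BPI. They speak of worst and average pain, they refer to questionnaires, and the BPI is the questionnaire named at baseline. On that reading the pain scale is consistent and the cell counts do not apply. This is plausible, and it is why response cannot be said to be clearly scored on the product. But the section also says that pain scores come from the table, and nothing limits that sentence to a descriptive use.

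A second reply is that a baseline narcotic record may be intended. The scoring sentence gives no timing, a no-increase condition presupposes a reference, and the content of Appendix 1 is not in the text at hand. That stands. A reader might infer that no baseline narcotic score exists; the text supports only that none is listed in the pretreatment evaluation.

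A third reply is that a statistical analysis plan can settle the scale. It can choose one, but it cannot supply a baseline product or narcotic grade that was not recorded.

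A reader might also infer from the counts that partial response is almost automatic in severe pain and impossible in mild pain. Neither follows:

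- The fall must hold at two assessments in a row without a rise in narcotic use, and a count of cells is not a response probability. The Background reports that in the earlier RTOG trial patients with high initial scores were less likely to respond, so the direction of any bias is not established.
- Mild pain (S = 1) can qualify: 4 to 2, 3 to 1 and 2 to 0 are all 2-point falls. Only the cell with product 1 is barred from partial response. If the product is read as the average score, that patient can still reach complete response at 0.

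**Conclusion.** The point holds as a conflict between the Pretreatment Evaluation and Assessment of Response sections, and it bears on the primary endpoint. The scale of the 2-point rule is unresolved. If follow-up is scored on the product, change from the scheduled baseline has no common scale. On either reading, the narcotic condition and narcotic relief lack a scheduled pretreatment reference.

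The figures (9 of 16 cells, or 6 of 12 if severity ends at 3; no partial response from a product of 1) are conditional on the product being the response scale. They show that 2 points has no constant meaning there. They do not measure bias in the response rate, and no stated sample size or power is affected. The documents also do not show that eligibility has to change: a consistent instrument and a stated rule for low baseline scores are enough.

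**What to change.** - Reconcile the two sections by naming one instrument and item for baseline and for every follow-up. BPI worst pain is the natural choice, because the BPI is already collected before treatment and the response rules speak of worst pain. This assumes that the BPI form in use has a worst-pain item; the form is not shown.
- Tie the complete-response, partial-response and no-response rules to that instrument. State for each which item it uses, including whether complete response stays on average pain.
- Add the analgesia type grade and frequency grade to the pretreatment evaluation, so that the narcotic score has a baseline.
- If the product pain score is kept as a secondary description, record it at baseline too.
- Report patients whose baseline score is below 2 as not assessable for partial response, and leave eligibility as it is.

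Cost: wording changes and two short analgesia grades at baseline, plus the two pain grades if the product score is kept.

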A PILOT STUDY OF CONCURRENT CAPECITABINE ( XELODA ) AND EXTERNAL BEAM RADIOTHERAPY FOR OSSEOUS METASTASES FROM BREAST CANCER.

BACKGROUND

Much of the clinical practice of oncology involves palliative care. In this setting ,the emphasis is on alleviation of symptoms and preservation or improvement of quality of life. A large body of clinical evidence documents the effectiveness of local-field external beam radiotherapy in palliation of pain from osseous metastases (1). Despite this general agreement, controversy remains regarding the optimal dose and fractionation schedule. Prospective phase III clinical trials (2-6), today, have failed to demonstrate superiority of one schedule over another ,and as a result, the patterns of practice of remain diverse in duration and intensity.

Between 1974 and 1980 the RTOG conducted a large national study to determine the effectiveness of five different dose fractionation schedules(2). A total of 1016 patients were entered ,266 into a “solitary metastasis” stratum, and 750 into a ”multiple metastasis “ stratum. The former were randomly assigned to treatment with 40,5Gy in 15 fractions or 20Gy in 5 fractions. The latter were assigned to 30Gy in 10 fractions, 15 Gy in5 fractions ,20 Gy in 5 fractions, or 25 Gy in 5 fractions. A quantitative measure of pain ,based on severity and frequency of pain, and the type and frequency of pain medications used, was devised to evaluate response. Overall, 89% of patients experienced minimal relief. There were no significant difference between the treatment arms in both strata. The initial pain score was found to be a useful predictor ; patients with high score were less likely to respond and were less likely to experience a complete response. Patients with breast and prostate cancer were significantly more likely to respond than patients with lung or other primary lesions. Patients completing their treatment as planned had significantly higher rates of complete response than those who did not .While some relief was experienced almost invariably within the first four weeks, complete relief was first reported later than four weeks after start of treatment in about 50 % of patients .The median duration of minimal and complete pain relief was 20 and 12 weeks ,respectively. There were no significant differences in duration of pain relief between the different arms It was concluded that all treatment dose schedules were equally effective.

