**Radiation Dose**

All patients will receive radiotherapy to a dose 30 Gy in 10fractions (3 Gy per fraction) over two weeks.

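### Follow-up ends 8 weeks after radiotherapy, too short to estimate the duration named in the primary objective or to confirm a complete response first seen at the last visit

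*Protocol*

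**What the plan says.** The primary objective in OBJECTIVES is "To determine the frequency and duration of pain relief and narcotic relief for the proposed regimen". Under Assessment of Response, questionnaires are given at "2, 4 and 8 weeks after completion of radiotherapy and by phone call interviews". The calls are qualified as "when necessary for completeness) in poor compliance patients", so they recover missed visits and do not lengthen follow-up. No later assessment appears anywhere in the Protocol. Radiation Dose sets the course at 10 fractions ("3 Gy per fraction) over two weeks").

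Both grades of response need two assessments in a row. Complete response "is defined as an average pain score of 0 for two consecutive analysis periods"; partial response is "A decrease of at least 2 points in the worst pain score for two consecutive analysis periods". A rise of at least 2 points after an earlier drop must appear on two successive questionnaires, but this rule is listed among the No response criteria.

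From the earlier multi-schedule radiotherapy trial, the Background reports: "The median duration of minimal and complete pain relief was 20 and 12 weeks", in that order. It adds that "complete relief was first reported later than four weeks after start of treatment in about 50 % of patients".

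**The concern.** The visit calendar and the primary objective do not fit together. The Protocol's own background leads one to expect relief lasting 12 to 20 weeks, while the whole period from the first fraction to the last questionnaire is about 10 weeks. Duration would then be reported mainly as censored values, and a regimen that prolonged relief would be no easier to recognise than one that did not.

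Frequency is affected too. Complete relief is the outcome named in the hypothesis and, on the Background's account, often comes late. A patient whose score first reaches 0 at the final visit has no second period in which to qualify, however lasting the relief. The calendar therefore lowers the count of complete responders. Data of either kind that were not collected on time cannot be recovered at analysis.

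**Working it through.** The Protocol gives no sample size or duration estimate to reproduce, so the check sets the calendar against the cited figures.

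**Visit times.** 2 weeks of radiotherapy plus 2, 4 and 8 weeks gives weeks 4, 6 and 10 from the start. First to last visit: 10 − 4 = 6 weeks. Day 1 to last visit: 10 weeks.

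**Reaching the median.** If the median is 12 or 20 weeks, at least half of the durations are that long or longer. Both medians exceed 10 weeks, so at least half of responders are still in relief when observation stops, whatever the shape of the distribution.

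**Share censored.** Assuming exponential durations, the share still in relief after a window of w weeks is 2^(−w/median).

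| Window | Median 12 weeks (complete) | Median 20 weeks (minimal) |
|---|---|---|
| 4 weeks (response first seen at the 4-week visit) | 2^(−4/12) = 0.794 | 2^(−4/20) = 0.871 |
| 6 weeks (first seen at the 2-week visit) | 2^(−6/12) = 0.707 | 2^(−6/20) = 0.812 |
| 10 weeks (relief from day 1) | 2^(−10/12) = 0.561 | 2^(−10/20) = 0.707 |

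The 10-week row is the most favourable case. A response first seen at the last visit has no window at all.

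**What three visits can show.** Write R for a visit meeting the response criterion and N for one that does not. Two consecutive Rs occur in three patterns: RRR, RRN and NRR. None leaves room for two later Ns, so 0 of 3 can show both a two-period response and a two-questionnaire rise. RRN shows a loss of relief once, at the 8-week visit. With four visits, 1 of 8 qualifying patterns can show both; with five, 4 of 19.

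**Complete responses first seen at the last visit.** The Protocol gives one point on the onset curve: about half later than 4 weeks from the start. As an illustration only, assume Weibull onset with median 4 weeks and shape k, so F(t) = 1 − 2^(−(t/4)^k), and assume relief persists to the next visit. The share of patients in complete response by the last visit who first show it there is [F(10) − F(6)] / F(10).

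- k = 0.8: (0.764 − 0.617)/0.764 = 0.19
- k = 1: (0.823 − 0.646)/0.823 = 0.21
- k = 1.5: (0.935 − 0.720)/0.935 = 0.23
- k = 2: (0.987 − 0.790)/0.987 = 0.20

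**Follow-up needed.** With onset at the first visit (week 4), the cited medians fall at 4 + 12 = week 16 and 4 + 20 = week 24 from the start, that is 14 and 22 weeks after radiotherapy. With onset at week 10 they fall at 20 and 28 weeks after radiotherapy.

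**The case against.** The strongest reply is that duration is right-censored, not unobservable. A patient in response at 2 and 4 weeks whose pain has returned at 8 weeks is an observed loss, and the proportion still in response at 8 weeks can be estimated. This stands. A reader might infer that duration cannot be measured at all; the Protocol does not support that.

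A reader might also infer that a relapse can never count because it cannot be seen twice. The two-questionnaire rise is a No response criterion. The Protocol does not call it the end of relief, and an analysis plan could let a single rise end the duration. That plan could also settle censoring and deaths, but it cannot supply visits that were never scheduled.

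Nor does it follow that the half of complete responses starting after four weeks is lost. One first seen at the 4-week visit can be confirmed at 8 weeks; only those first seen at 8 weeks are caught. The percentages for them come from an assumed curve.

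Finally, this is a pilot meant to gather preliminary data, in patients who need only a 3-month life expectancy to enter and who receive systemic capecitabine. Later calls will meet deaths and treatment changes that blur attribution. That is a fair limit on what longer follow-up can show, but it does not reconcile a stated primary objective with a calendar shorter than the durations the Protocol cites.

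**Conclusion.** The point holds in this form. At the durations cited in the Background, most responders would be censored: about 71% (complete) or 81% (minimal) over 6 weeks, and 56% or 71% over 10 weeks. These percentages assume exponential durations. That no median would be reached needs only the cited medians to apply to this regimen; markedly shorter relief would be seen more often.

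Complete response frequency is biased down, because a response first seen at 8 weeks cannot qualify. The Protocol does not give the size of this loss. The illustrative 19–23% is the share with no opportunity for confirmation, under an assumed Weibull onset. Some of those patients would have failed confirmation anyway, so it is not an estimate of the bias itself. Partial response, complete response first seen by the 4-week visit, and early loss of relief remain assessable.

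**What to change.** Preferred: amend Assessment of Response to add later telephone questionnaires, a mode the Protocol already uses. At least one should follow the 8-week visit closely enough to confirm a response first seen there. The rest should run beyond about 14 weeks after radiotherapy for complete relief and 22 weeks for minimal relief; later onset needs longer. The amendment should also say what ends a period of relief. The cost is an amendment and a few short calls per patient, with some loss to death or treatment change.

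Otherwise: remove duration from the primary objective and report the proportion still in response at 8 weeks. State that complete responses first seen at 8 weeks are unconfirmed, and report them separately. This costs a wording change and gives up any estimate of median duration.
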